### Criteria for discontinuing or modifying allocated interventions {11b}

Since participation in this study is voluntary, patients may discontinue the intervention at any time, as explained during the informed consent process. From a clinical perspective, the study intervention will be discontinued under the following circumstances:Emergence of severe adverse reactions such as sustained dissociation, suicidal ideation, or emotional dysregulation that temporarily make the patient unresponsive to EMDR therapy—in such cases, therapy will pause to focus on resource-building and stabilization before potentially resuming.Severe non-compliance, defined as missing more than four consecutive sessions without contact.Therapist deviation from the given therapy protocol, as identified during mid-therapy fidelity inspections.

At the time of discontinuation, the following data will be collected to assist in planning the selection of future patients:The point in time when discontinuation occurred.The reason(s) for discontinuation, and when possible, the primary endpoint assessment and existing depressive symptom severity.

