## Methods: participants, interventions, and outcomes

### Study setting {9}

The present study will be conducted across multiple settings corresponding to the sequential three phases of the research.i.Phase one will be conducted through a narrative literature review, expert consultations (involving EMDR therapists) based in Pakistan. These activities will be carried out through a combination of in-person meetings and secure online platforms, depending on participant availability.ii.Phase two will be implemented in both online and in-person clinical settings at the selected clinics or psychotherapy centers located in the three selected cities in Pakistan, where the adapted DeprEnd EMDR therapy protocol will be delivered by four EMDR certified therapists. Data collection during this phase will occur through clinical assessments and standardized self-report measures.iii.Finally, phase three will be conducted as a multi-center randomized controlled trial study implemented in both online and in-person clinical settings at the selected clinics or psychotherapy centers located in the three selected cities in Pakistan, where the adapted DeprEnd EMDR therapy protocol will be delivered by four EMDR certified therapists. Data collection during this phase will occur through clinical assessments and standardized self-report measures. During this phase, process fidelity and adherence to the adapted DeprEnd EMDR protocol will be monitored at mid of therapy. 

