### Methods for addressing non-adherence and missing data {20c}

To account for protocol deviations, primary analyses will employ both intention-to-treat and per-protocol approaches, with the intention-to-treat population including all randomized participants regardless of adherence and the per-protocol population restricted to those completing ≥ 80% of sessions with verified fidelity. For missing data, a tiered strategy will be implemented:Continuous monitoring with initiated outreach after any missed assessment to minimize attrition.Multiple imputation by chained equations using 50 imputed datasets incorporating baseline characteristics, treatment arm, and observed outcome trajectories as predictors.Sensitivity analyses comparing results with pattern-mixture models that assume different missingness mechanisms (missing at random vs. not at random).

For participants who discontinue therapy but complete all outcome assessments, their available data will be included in the mixed-effects models used for longitudinal analyses.

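### Therapist deviation is listed as a reason to discontinue a client's therapy; make it a trigger for correcting the therapist while the client normally continues

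*Protocol article*

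**What the plan says.** Section {11b} of the protocol article opens its list with "the study intervention will be discontinued under the following circumstances". Three items follow.

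- Severe adverse reactions, for which "therapy will pause to focus on resource-building and stabilization before potentially resuming".
- Severe non-compliance, defined as more than four sessions missed in a row with no contact.
- "Therapist deviation from the given therapy protocol, as identified during mid-therapy fidelity inspections", with nothing further.

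At discontinuation the same section collects the time, the reason and, "when possible, the primary endpoint assessment and existing depressive symptom severity". The stated purpose is to help plan the selection of future patients.

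Other sections bear on the point:

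- **Study setting {9}:** "process fidelity and adherence to the adapted DeprEnd EMDR protocol will be monitored at mid of therapy", and the therapy "will be delivered by four EMDR certified therapists". Participant timeline {13} places the fidelity evaluation at T2.
- **Strategies to improve adherence {11c}:** a fidelity analysis after 40 treated patients leads to corrective measures where deviations are found, and random video audits run throughout.
- **Non-adherence and missing data {20c}:** intention-to-treat covers everyone randomized. Per-protocol needs at least 80% "of sessions with verified fidelity". It adds: "For participants who discontinue therapy but complete all outcome assessments, their available data will be included in the mixed-effects models used for longitudinal analyses".

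**The concern.** The first two items in the list describe the client's condition or behaviour, and each is qualified, one by a pause and the other by a threshold. The third describes the therapist's conduct and has no qualification. Followed as written, a client who entered with a HAM-D-17 score of at least 20 would lose the rest of the course because the therapist drifted from the manual.

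Two things are at stake. The first is care: treatment is withdrawn for a reason that has nothing to do with the client's state. The second is interpretation: the intention-to-treat comparison of online with in-person delivery would include shortened courses produced by a protocol rule and not by either mode of delivery. Because all therapy comes from four therapists, one therapist's drift could affect several clients.

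**Working it through.** The plan gives no figure for this point, so the check is mainly a comparison of sections, with a little arithmetic on dose.

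**1. Is stopping the plain reading?** The governing verb in {11b} is discontinue. Only the adverse-reaction item softens it to a pause. The deviation item has neither that softening nor a threshold. Stopping is therefore the plain reading, though not the only possible one.

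**2. What does a stopped client lose?** Inputs: 10 to 14 weekly sessions (Intervention description {11a}) and an inspection at mid-therapy ({9}, {13}). Assumption: mid-therapy means half the sessions.

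- Sessions not delivered: 10/2 = 5, up to 14/2 = 7, which is 50% of the course.
- Weeks from stopping to the planned end, at one session a week: 10 − 5 = 5, up to 14 − 7 = 7. A rating taken at the stop is thus about 5 to 7 weeks earlier than T3, while the primary endpoint (Outcomes {12}) is change from T01 to T03.

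**3. Does the analysis need the stop?** No. Per-protocol membership already requires verified fidelity, so a client whose fidelity check fails is dealt with there. Intention-to-treat keeps the client in either case. The stop changes the treatment received and does nothing for either analysis set.

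**4. Which way would the non-inferiority estimate move?** The contrast is online minus in-person change, with non-inferiority concluded if the upper confidence bound is below 3 points ({20a}). Let p be the share of clients stopped in an arm and c the HAM-D-17 points lost by stopping.

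- Unequal stopping with a common c: shift = c × (p_online − p_in-person). The arm with more stops looks worse.
- Equal stopping: if a true mode difference D builds up evenly over sessions (an assumption), a halfway stop leaves D/2, and the estimate becomes D(1 − p) + pD/2 = D(1 − p/2). The difference is blurred, which leans towards concluding non-inferiority.

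The article gives neither p nor c, so no number can be put on either case.

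**5. Does the stated sample size change?** No. (1.96 + 0.84)² × 128 / 25 = 7.84 × 128 / 25 = 40.14, and 80/0.85 = 94.1, which agree with the stated 40 per arm and 94 recruited. The rewording affects neither.

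**The case against.** The strongest reply is that the list is loosely worded and correction was meant. The section heading also covers modifying, the first item under the same lead-in is only a pause, and {11c} shows that the trial's usual answer to a deviation is correction. This has force, and it rules out calling the sections contradictory. It does not remove the point. The corrective measures in {11c} are attached to the review after 40 patients, and nothing there says that the affected client's therapy goes on. If correction was meant, the change simply says so.

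A reader might infer that stopped clients lose their T3 and T4 values. The article does not support that. No section ends assessment when therapy stops, {18a} schedules four timepoints without exception, and {20c} plans outreach after a missed assessment, multiple imputation and pattern-mixture models, and foresees discontinuers who complete every assessment. What remains is that completion is foreseen but not required.

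A reader might also calculate lost power. Using power = Φ(5/(8√(2/n)) − 1.96), suppose a further 5%, 10% or 25% of clients had no T3 after 15% dropout. Then 94 × 0.85 × 0.95, × 0.90 or × 0.75 leaves about 76, 72 or 60 clients, and power falls from 0.80 to about 0.78, 0.75 or 0.68. These figures need an invented stop rate and missing T3 values, and they use the five-point planning difference and not the 3-point margin. They are not evidence of a loss.

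On harm to the client, {30} and {34} provide post-trial care, including referral of non-responders. That softens the consequence but does not justify the trigger.

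**Conclusion.** The point holds as a badly fixed rule that is worth changing, with moderate confidence. As written, {11b} cuts a client's course by about half because of what the therapist did, and neither analysis set needs it. The 50% figure rests on taking mid-therapy as the halfway session.

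The trial-level effect is unknown in size and direction and is probably small. It would be wrong to say that the rule biases the trial towards non-inferiority: that follows only if stops are balanced between arms and a real mode difference exists, and the article shows neither. Nor does the rule breach intention-to-treat, which defines who is analysed and not how long a client is treated. There is also no added per-protocol loss, since a failed fidelity check already decides that membership.

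**What to change.** Remove therapist deviation from the discontinuation list in {11b} and state instead:

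> A therapist deviation found at a fidelity inspection triggers corrective measures for the therapist (see {11c}). The client's therapy continues unless continuing is judged clinically unsafe, and the scheduled T3 and T4 assessments are attempted in every case. For analysis, the deviation affects per-protocol membership and not intention-to-treat inclusion; it is logged by arm and remains subject to data monitoring committee review and audit.

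The safety exception keeps clinical discretion. The last clause keeps the text consistent with the committee's review of deviations in {21a} and the targeted audits in {23}. Transfer to another trial therapist in the same arm can be an option, but four therapists over three cities is 4/3 = 1.3 per city, so it may not be available in person.

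The cost is some supervision time and one log field. Continuing the client uses only sessions already planned. If the change is classed as major, {25} requires ethics approval first. For clients already treated, recording past fidelity failures by arm, with the action taken, would show whether the rule was ever applied.

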### Clients selection and sample size {14}

The study focuses on individuals with MDD in Pakistan, specifically selecting geographically accessible participants residing in the major cities of Rawalpindi, Islamabad, and Peshawar. Recent literature cites various studies such as by Ishtiaq et al. [56], Noor et al. [57] and Umar et al. [58] on the high prevalence of depressive disorders in these three cities of Pakistan. However, since the exact number of MDD cases in these three major cities is unknown, a more customized, multi-stage sampling procedure has been adopted.

Initially, three rehabilitation centers located in the selected cities will be randomly but purposively picked for recruiting patients. The centers will not be chosen fully at random; rather, the characteristics of the vicinity and patient flow into centers will be considered. Within each selected center, clients will be recruited using a sequential consecutive sampling technique with a rolling enrollment strategy. This approach involves selecting every eligible patient who meets the inclusion criteria until the required sample size is achieved [59]. The estimated sample size of (*n* = 80) was calculated by using the below given approximation method for two independent group means, as recommended in the existing literature by Sakpal [60] and Chow [61]:$$n=\frac{\left({Z}_{\frac{\alpha }{2}}+{Z}_{\beta }{)}^{2}\cdot (2{\sigma }^{2}\right)}{\left({M}_{1}-{M}_{2}{)}^{2}\right.}$$where.

*n*= is the estimated sample size.

Zα/2 = is the Z-score matching to the desired α level (for e.g., 1.96 for 95% confidence).

Z*β* = is the Z-score matching the desired power level (for e.g., 0.84 for 80% power).

σ^2^ = is the pooled variance of two groups.

µ​_1_ - µ​_2_= are the expected difference in means of depression scores.

A two-sided significance level of α = 0.05 was selected, consistent with conventional recommendations for clinical trials, resulting in α/2 = 0.025 and a corresponding Z-score of 1.96. Statistical power was set at 80% (1 − β = 0.80), yielding β = 0.20 and a corresponding Z-score of 0.84.

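### Discontinuation data are assigned to planning patient selection and never tied to the outcome analysis, and the main imputation model leaves stopping out

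*Protocol article*

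**What the plan says.** In the Protocol article, Criteria for discontinuing or modifying allocated interventions {11b}, the data taken when a client stops are introduced with the words "the following data will be collected to assist in planning the selection of future patients". The items are the time of stopping and "The reason(s) for discontinuation, and when possible, the primary endpoint assessment and existing depressive symptom severity". No other use is stated there or elsewhere.

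Clients selection and sample size {14} describes consecutive, rolling enrolment: "This approach involves selecting every eligible patient who meets the inclusion criteria until the required sample size is achieved".

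Methods for addressing non-adherence and missing data {20c} makes these provisions:
- an analysis set described as "the intention-to-treat population including all randomized participants regardless of adherence", alongside a per-protocol set;
- for missing scores, "Multiple imputation by chained equations using 50 imputed datasets incorporating baseline characteristics, treatment arm, and observed outcome trajectories as predictors";
- "Sensitivity analyses comparing results with pattern-mixture models that assume different missingness mechanisms (missing at random vs. not at random");
- for those who stop treatment but stay in assessment, "For participants who discontinue therapy but complete all outcome assessments, their available data will be included in the mixed-effects models used for longitudinal analyses".

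**The concern.** There are two separate problems.

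**Purpose.** While recruitment is still open, using the reasons why clients stopped to plan whom to select next does not fit with taking every eligible client. {11b} does not say whether it means this trial or later work.

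**Analysis.** Stopping is likely to carry prognosis. The reasons listed in {11b} include severe adverse reactions and prolonged non-attendance. Time and reason of stopping are collected, and session attendance is already used in the exploratory dose–response analysis in {20b}. None of these is among the predictors named for the main imputation. The primary question is non-inferiority of online delivery, so if stopping is more frequent online, or has a worse prognosis there, over-favourable imputation pushes the estimate towards the conclusion the trial hopes to reach.

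**Working it through.** **The plan's own figures.** With SD 8, difference 5, two-sided alpha 0.05 and 80% power ({14}), n = (1.96 + 0.84)² × 2 × 8² / 5² = 7.84 × 128 / 25 = 40.14 per arm, against the stated 40. Recruitment: 80 / 0.85 = 94.1, against the stated 94. These reproduce and are not in dispute here. They supply the SD, the arm size and the planned 15% dropout.

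**What the main imputation does with a stopper.** Take two clients in the same arm with the same baseline and T2 scores. One continues to T3. The other stops after T2 and has no later score. Every predictor listed in {20c} is identical for the two, so their T3 scores are predicted from the same distribution. If a severity score was obtained at stopping, it can count as part of the observed trajectory and the two clients then differ. {11b} promises that score only where it can be obtained.

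**Bias formula.** Let p be the share of T3 scores imputed in an arm, and d the number of points by which stoppers are truly worse than imputed. The online-minus-in-person difference (positive = online worse) is then understated by

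p_online × d_online − p_in-person × d_in-person.

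The documents give neither the split of dropout by arm nor d. Both are assumptions.

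| Missing T3, online / in person | d | Shift towards online (points) | Share of 3-point margin |
|---|---|---|---|
| 15% / 15% | same in both arms | 0 | 0% |
| 20% / 10% | 3, same in both arms | 0.10 × 3 = 0.3 | 10% |
| 20% / 10% | 8, same in both arms | 0.10 × 8 = 0.8 | 27% |
| 15% / 15% | 2 to 8, online only | 0.15 × d = 0.30 to 1.20 | 10% to 40% |

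The 20%/10% split averages to the planned 15%.

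**Effect on the non-inferiority decision.** With SD 8 and 40 per arm, SE = 8 × √(2/40) = 1.789. Non-inferiority is concluded when the upper 95% limit is below 3 ({20a}). If the estimate is centred at μ, the probability is Φ((3 − μ)/1.789 − 1.96). For a true loss of exactly 3 points:
- no bias, μ = 3.0: Φ(−1.96) = 2.5%
- shift 0.3, μ = 2.7: Φ(0.168 − 1.96) = 3.7%
- shift 0.5, μ = 2.5: Φ(0.280 − 1.96) = 4.6%
- shift 0.8, μ = 2.2: Φ(0.447 − 1.96) = 6.5%

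**Numbers of stoppers.** With 94 randomised, about 47 per arm, the assumed rates give 0.20 × 47 ≈ 9 online and 0.10 × 47 ≈ 5 in person without T3. This limits how finely stopping can be modelled.

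**The case against.** **Enrolment drift.** A reader might infer that recruitment will move away from clients who do badly online and so bias the comparison. The documents do not support that. The phrase about future patients may mean later studies. {11b} sets no selection rule. {14} and {15} keep consecutive enrolment, and {25} requires ethics approval before eligibility criteria change. Eligibility is confirmed before allocation ({16c}), so any drift would act on both arms. It would change the population studied without unbalancing the arms, and could move the contrast only through a trait that modifies the effect of delivery mode. None is shown. What stands is the conflict of wording with {14} under one natural reading. {10} also leaves some discretion, since being treatment-naive is only a preference.

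**Informative stopping ignored.** A reader might also infer that the plan treats stopping as uninformative throughout. It does not. {20c} plans not-at-random pattern-mixture analyses, outreach after any missed assessment, an intention-to-treat set of all randomised clients, and use of outcomes from those who stop but remain assessed. A missing-at-random primary analysis with such sensitivity analyses is an accepted structure. What stands is narrower: the main estimate does not use stopping information that the trial already collects.

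**Detail left to an analysis plan.** A full predictor list could reasonably sit in a statistical analysis plan that is not shown. But {20c} does state the predictors, and an analysis plan would not correct the purpose stated in {11b}.

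**Size.** The 20%/10% split and the 3 to 8 point deficit are assumed. The deficit must remain after conditioning on arm and earlier scores, and its upper end equals the full planning SD. This is fair, and the figures should be read as an illustration.

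**Conclusion.** The point holds in limited form. The purpose in {11b} is wrongly stated for a trial that is still recruiting, or at best ambiguous, and it should be reconciled with {14}. The main imputation in {20c} omits stopping and attendance, so stoppers without a later score are imputed as continuers.

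The resulting bias is near zero if stopping is alike in both arms. Under the assumed 20% versus 10% missing T3 and a 3 to 8 point deficit, it is 0.3 to 0.8 points towards non-inferiority, with false non-inferiority of 3.7% to 6.5% in place of 2.5% (SD 8, 40 per arm, true loss of 3 points). The documents establish neither that stopping will differ by arm nor that enrolment will drift. The case for acting is that the correction is cheap and that, if online stopping is more frequent or more adverse, the error favours the trial's hypothesis.

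**What to change.** **In {11b}:**
- State that time, reason and severity at discontinuation are collected for the intention-to-treat and missing-data analyses.
- State that eligibility will not be changed or applied differently in this trial because of them.
- Say that the scheduled T3 assessment will be sought from everyone who stops therapy. The endpoint assessment now described is taken at the time of stopping and is not necessarily a T3 score.

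**In {20c}:**
- Add sessions attended and discontinuation status and time to the chained-equations model as auxiliary variables.
- Include any severity score taken at stopping.
- Use the reason for stopping to define the patterns in the not-at-random sensitivity analysis. With roughly 9 and 5 clients lacking T3 under the rates assumed above, and reason undefined for those who continue, it would be too sparse as an imputation predictor.

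**Cost:** a few sentences, variables largely collected already, and the effort of obtaining T3 from those who stop. Intervals may be somewhat wider, and the effect of stopping will be weakly estimated if few stoppers have an observed T3.

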### Strategies to improve adherence to interventions {11c}

To optimize adherence to the intervention protocols, several strategies will be implemented.First, before beginning therapy sessions, all participating therapists will receive comprehensive training in the adapted DeprEnd EMDR protocol. This training will be given at least for a week, and it will include orientation about the adapted therapy protocol and practical demonstration of eight steps of the protocol. It will enable the therapists to learn how to administer the adapted therapy protocol.Second, patients will undergo thorough psychoeducation both before and during treatment to enhance their motivation and therapy compliance. The psychoeducation will include guidance about EMDR therapy, trauma, depression, the significance of therapy, and various resources related exercises.Third, midway through the study (after completing therapies for 40 patients), a comprehensive fidelity analysis will be conducted to assess overall adherence to the treatment process, with corrective measures implemented if any deviations are identified; throughout the therapy period, regular fidelity checks will also be performed through random video audits of sessions.Fourth, a flexible scheduling system will accommodate reasonable timing adjustments, particularly for online therapies, which will be scheduled according to client preferences. For clients showing early signs of non-adherence (such as two consecutive missed sessions), follow-up mobile calls or in-person contacts will be made with the clients or their family members to address potential barriers and encourage continued participation. Additionally, clients will have the option to reschedule missed sessions within a reasonable timeframe to ensure continuity of care. This proactive approach aims to support clients in overcoming obstacles and maintaining engagement in their therapy.

